
A 2018 systematic review concluded that available data do not support the superiority of one of the eGFR equations in measuring or predicting functional decline [17]. Estimating equations based on serum creatinine may overestimate GFR. Elevated cystatin C levels may indicate persistent chronic inflammation, which cannot be detected by elevated C reactive protein levels. There is only one study, which measured GFR (mGFR, ^125^I-iothalamate clearance) to study kidney function on self-reported frailty. The authors found an inverse association between both parameters. However, the data are difficult to interpret because frailty was not assessed by objective geriatric assessment tests [18]. There are no studies on the impact of reduced kidney function on frailty that involve long-term, population-based, epidemiological cohorts. Together, all the above studied relied on surrogate markers of kidney function rather than direct GFR measurements. Thus, we will perform a prospective, longitudinal, observational SHIP-AGE/MV-FIT study. A SPIRIT schedule and overview of the study design can be found in Fig 1. This study will implement direct measurements of GFR by the iohexol method (mGFR) to evaluate the impact of CKD in multi-component “real world” primary care strategies on lowering frailty among elderly persons in MV. We will study two groups of individuals; i.e. individuals aged 65 years or older with (i) directly measured GFR (mGFR) >60 mL/min and (ii) with mGFR 30-60 mL/min (KDIGO Stage 3) (Fig 2). All participants will undergo multi-component intervention strategies (multi-factorial geriatric assessment, monitoring and management systems (Fig 3) to clarify the impact of CKD on frailty in conditions of “best primary care” to reduce frailty and incident falls in the elderly [2, 19].

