### Eligibility criteria

Inclusion/exclusion criteria were made as simple as possible to recruit a largely heterogeneous (“real world”) elderly population.

Inclusion Criteria: Age 65 years or older, mGFR >30 mL/min per $1.73\;{\text{m}}^{2}$, being able to understand and give written informed consent.Exclusion Criteria: Bedridden, palliative, inability to consent, severe dementia, inability to speak, lack of compliance (paracusis, inability to fulfill at least 60% of the assessments).

Recruitment is promoted through various regional media and communication channels. These include advertisements in local newspapers, publications in municipal bulletins, flyers, and information on websites and digital platforms. Additionally, local networks and community structures are utilized to reach interested older adults and encourage broad participation. We will establish networks with ambulatory practices and stakeholders to recruit and follow the patients. In terms of CKD patients, we will contact local nephrologists in practice. All sites are located in MV.

Participants will be stratified by mGFR: into (a) individuals with mGFR, 30-60 mL/min per 1.73 m2 or urine albumin/creatinine ratio (UAC) ≥300 mg/g and (b) individuals with mGFR, >60 mL/min per $1.73\;{\text{m}}^{2}$ and urine albumin/creatinine ratio (UAC) <300 mg/g. Approximately 328 participants (40%) are expected to have mGFR, 30-60 mL/min per $1.73\;{\text{m}}^{2}$ and 492 participants (60%) are expected to have mGFR, >60 ml/min/$1.73\;{\text{m}}^{2}$ (Fig 2). The planned minimum follow-up duration for participants is three years, while the maximum follow-up duration is approximately six years.

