### Sample size

We performed a sample size calculation for the SHIP-AGE/MV-FIT cohort. A 3-year prevalence of frailty of 20% is expected in individuals with mGFR 30-60 mL/min per $1.73\;{\text{m}}^{2}$ and a prevalence of 12.5% in individuals with mGFR >60 ml/min/1.73 m2. The effect size of the GFR group on frailty is expressed by the odds ratio (OR) between mGFR-group 30-60 mL/min per $1.73\;{\text{m}}^{2}$ compared to the reference group mGFR >60 mL/min per $1.73\;{\text{m}}^{2}$. In multivariable adjusted models with frailty as independent variable, OR per 10 mL/min/$1.73\;{\text{m}}^{2}$ decrease of mGFR was reported to be 1.2 (Cardiovascular Heart Study) [14] and 1.4 (Modification of Diet in Renal Disease study) [18]. An OR of 1.83 was reported in multivariable logistic regression analysis when comparing mGFR 30-44 to ≥45 mL/min per $1.73\;{\text{m}}^{2}$. The target sample size was computed with G*Power by expecting a multivariable adjusted effect size of OR=1.75 in logistic regression analysis with 3-year frailty as the binary response variable. Statistical power was set to 80%, type I error rate was set to 5% and group imbalance is expected (40% will have mGFR, 30-60 mL/min per $1.73\;{\text{m}}^{2}$). Under these conditions one-sided testing led to the required sample size of 616 individuals to be analysed. To further adjust for drop-outs (lost-to-follow-up, deaths, no longer willing or capable to participate in the study), the sample size was corrected for a 25% drop-out rate justifying that 820 volunteers will be enrolled at baseline. The overall goal for recruitment is 820 participants, although the final enrolment number may be between 700 and 1,000.

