### Statistical methods

Evaluation of the impact of CKD on frailty among elderly persons The primary outcome Frail vs. non-Frail and events observed in the follow-up period will be analyzed using multivariable logistic regression. Furthermore, in case of proportional hazards, multivariable Cox regression analysis will be conducted to study the time to frail, which usually has a higher statistical power than logistic regression. Main exposure variables that enter both models are mGFR at baseline, pre-existing frails, frailty-index, sex, BMI, age, comorbidities/medical history, medication, geriatric depression score, and quality of life (see assessments). In univariable analysis all possible predictor variable will be checked in relation to the response variable whether a transformation of axis (e.g. log-transformation), spline-usage, or (re-)categorization seems appropriate and medically plausible for the use in multivariable models. In case of mGFR, we include baseline measurements, gender-specific quantile probabilities, and absolute and relative mGFR changes if available. Interaction terms will be used in model equations based on prior knowledge (evident interactions) and other (currently unknown) interaction effects will be tested for a significant increase in the model performance. Event variables (obligation to dialysis, hospital re-admission, referrals to nursing homes, all-cause mortality, etc) will be analyzed with penalized multivariable logistic regression. In order to create complete cases, we make use of imputed datasets (e.g. by Multiple imputation using Fully Conditional Specification or by Random Forest imputation). The model size will be controlled by setting regularization parameters (Elastic net or LASSO) and repeated internal cross-validation will be used to avoid overfitting and to generate more robust estimates that can result in a very generalizable model. Secondary endpoints such as the patient-individual changes in mGFR and in the frailty score will be analyzed in linear mixed effects models. Implementation of multi-component healthcare will be monitored by usage of the regional digital health records. If necessary, the results of formative process analysis are used to adapt processes or the documentation.

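### The CKD groups are defined in two incompatible ways, and the form of mGFR, the exposure under test, may be chosen after looking at frailty, so the test is not tied to the contrast that was powered

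*Protocol article*

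**What the plan says.** **Group definition.** Section 3 (Evidence and objectives) of the Protocol article sets up two groups by mGFR alone: "directly measured GFR (mGFR) >60 mL/min and (ii) with mGFR 30-60 mL/min (KDIGO Stage 3". Sample size uses the same split: "The effect size of the GFR group on frailty is expressed by the odds ratio (OR) between mGFR-group 30-60 mL/min" and a reference group above 60. Eligibility criteria stratifies differently. Its first stratum is "individuals with mGFR, 30-60 mL/min per 1.73 m2 or urine albumin/creatinine ratio (UAC) ≥300 mg/g", and its second requires both mGFR above 60 and a ratio below 300 mg/g. The same section then gives the expected split, 328 (40%) and 492 (60%), by mGFR alone.

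**Analysis.** Statistical methods states "Main exposure variables that enter both models are mGFR at baseline", followed by a list of covariates, and gives no scale for mGFR. For all predictors it says "In univariable analysis all possible predictor variable will be checked in relation to the response variable whether a transformation of axis" is needed, with the further options "spline-usage, or (re-)categorization seems appropriate and medically plausible for the use in multivariable models". The next sentence reads: "In case of mGFR, we include baseline measurements, gender-specific quantile probabilities, and absolute and relative mGFR changes if available". Nothing there names the 30-60 versus above-60 contrast as the primary term or exempts mGFR from the check against the response. Table 1 lists mGFR among the main confounders rather than as the exposure.

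**The concern.** Two separate things are at stake.

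First, who counts as exposed. Two analysts following different sections would put the same person in opposite groups and could report different CKD effects.

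Second, the validity of the main test. Choosing the shape of a nuisance covariate by looking at the outcome is common and often tolerable. Doing so for the one variable whose effect is being tested is different: the form that happens to fit best is then tested as if it had been fixed beforehand, and a nominal 5% test need not have a 5% error rate. The power statement also stops describing the planned test, because the sample size belongs to one specific contrast that the analysis does not commit to.

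**Working it through.** **1. The groupings side by side.** Take a participant with mGFR above 60 and a ratio of at least 300 mg/g.

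| Section | Rule | Group |
|---|---|---|
| 3. Evidence and objectives | mGFR only | above 60 |
| Sample size | mGFR only | reference |
| Eligibility criteria | mGFR or ratio | CKD stratum |

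The stated split is 0.40 × 820 = 328 and 0.60 × 820 = 492, both labelled by mGFR alone. Under the mGFR-or-ratio rule it would be 328 + k and 492 − k, where k is the number with mGFR above 60 and heavy albuminuria. The documents give no prevalence. At an assumed 0.7% to 4% of the 492, k is about 3 to 20.

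**2. Which contrast the sample size belongs to.** Inputs from Sample size: 12.5% and 20% frail, 40% exposed, 80% power, 5% one-sided.

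- OR = (0.20/0.80)/(0.125/0.875) = 1.75, as stated.
- Overall frailty rate = 0.4 × 0.20 + 0.6 × 0.125 = 0.155.
- Hsieh formula for a binary covariate with exposed share B: n = [z(α)·√(p(1−p)/B) + z(β)·√(p0(1−p0) + p1(1−p1)(1−B)/B)]² / [(p1−p0)²(1−B)].
- Numerator: [1.645·√(0.155 × 0.845/0.4) + 0.842·√(0.125 × 0.875 + 0.20 × 0.80 × 0.6/0.4)]² = [0.941 + 0.497]² ≈ 2.07.
- Denominator: 0.075² × 0.6 = 0.003375.
- n ≈ 613. Demidenko's Wald method gives 609, or 622 with variance correction. The stated 616 lies within this range. Two-sided versions give 774-790 and do not match.
- Power at 616, one-sided: 80.2%. Drop-out: 616/0.75 = 821.3, so 822 against 820 stated.

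The 616 thus reproduces for the binary mGFR contrast tested one-sided.

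**3. Type I error when the form is chosen on the outcome.** All simulations are under the null with n = 616 and about 15.5% frail. The mGFR distribution, its correlation with age, the prevalence of a ratio of 300 mg/g or more and the list of candidate forms are assumptions.

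| Procedure | Type I error |
|---|---|
| Two-group mGFR contrast, fixed in advance | 4.8% one-sided |
| Smaller p of the two group definitions | 5.7-6.5% one-sided, 5.1-6.0% two-sided |
| Best of six forms by AIC, no age adjustment | 11.6-12.4% one-sided |
| Form picked univariably, then tested adjusted for age and sex: three forms | about 6-10% two-sided |
| The same sequence: six forms | about 10-16% two-sided |

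In the second and third rows, the prevalence parameter for the ratio ran over 1-6% and the mGFR SD parameter over 12-22. The six forms in the third row are two groups by mGFR, two groups by mGFR or ratio, linear, log, sex-specific quartile trend and a three-knot spline. The last two rows follow the sequence that Statistical methods describes most closely.

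One three-form set (continuous, cut at 60, sex-specific quartiles), with mGFR SD 18, shows what drives the range:

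- Age strongly related to frailty (assumed OR 2 per SD; age-mGFR correlation −0.5 or −0.63): 5.6% and 6.3%, against 5.2-5.4% for a fixed continuous form.
- Age unrelated to frailty: about 9%.

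The simulation standard error with 3,000 runs is √(0.05 × 0.95/3000) ≈ 0.4 points, so the 5.6% is not clearly distinguishable from the fixed form.

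**The case against.** The strongest defence is that the plan does not say to take the smallest p-value. It asks for a form that is medically plausible, judged in univariable analysis, with the test made later in an adjusted model. If age drives much of the univariable association, the adjusted test inherits little of the selection, as the 5.6% and 6.3% show. The sentence on mGFR can also be read as listing several forms to be entered, not one to be picked. This limits the size. It does not remove the problem: plausibility narrows the choice without fixing it, mGFR is not exempted, and no reading names one primary term. Cross-validation and penalisation, also planned, address model size and overfitting; they do not correct the test of mGFR. Nor is this only detail left to a fuller document, since the article itself states the outcome-guided rule and both groupings.

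Four stronger readings are tempting, and the documents do not support them:

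- **Three conflicting definitions of CKD.** There are two. Sex-specific quantiles are a scale for analysis, not a definition of disease.
- **An error rate near 20%.** That figure appears only if cutpoints at 45, 60 and 75 and the lowest sex-specific quartile are added and the smallest p is taken. The protocol states neither that list nor that rule.
- **Splitting mGFR at 60 is itself an error that costs power.** The split is what was powered, and 616 reproduces for it. Against a linear truth, the answer depends on which cited effect is used: two-group power is 46-77% at an OR of 1.2 per 10 mL/min and 88-100% at 1.4 (assumed SD 14-22, age correlation −0.5, one-sided).
- **Albuminuria has no place in the exposure.** The central hypothesis concerns reduced kidney function, but the first objective concerns CKD. The documents require the sections to agree; they do not dictate which definition wins.

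**Conclusion.** The point holds in two parts. The group definitions contradict each other on the face of the text; this rests on no assumption. It matters mainly for who counts as exposed, since choosing between the two definitions adds at most about 1.5 points of one-sided error (6.5% against 5%).

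The larger statistical issue is that the form of mGFR is left to a check against frailty while the powered contrast is not named as primary. Any resulting error in the type I rate is upward. Its size is illustrative: about 6-10% with three forms and 10-16% with six, two-sided, with the low end close to nominal when few forms are considered and age strongly predicts frailty. The stated 80% power is correct for the two-group contrast but does not describe an analysis whose exposure term is still open.

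**What to change.** 1. Use one group definition in section 3, Eligibility criteria and Sample size. The choice consistent with the powering is mGFR 30-60 versus above 60, with the albumin/creatinine ratio as a separate baseline covariate. The alternative is to state the mGFR-or-ratio definition throughout and restate the expected split.
2. In Statistical methods, name that baseline two-group contrast as the single primary exposure term and exempt mGFR from the outcome-guided choice of form.
3. Keep continuous mGFR, a spline with preset knots and sex-specific quantiles as prespecified secondary or sensitivity analyses.
4. If a continuous term is preferred as primary, fix it in advance and recompute the power.

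The cost is wording and some loss of freedom to adapt the form of mGFR to the data. Recruitment opened on 2024-04-03 and the primary outcome is at 36 months, so on those dates no primary outcome is due before April 2027. A change made before then can still count as prespecified.

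### Unknown interactions are to be tested for significance within the primary models and no fixed primary model is set apart, so the single mGFR odds ratio and its 5% error rate are not secured

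*Protocol article*

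**What the plan says.** All of the following is in the protocol article.

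- **Primary analysis (Statistical methods).** "The primary outcome Frail vs. non-Frail and events observed in the follow-up period will be analyzed using multivariable logistic regression". A Cox model for time to frailty is added if hazards are proportional.
- **Variables (same section).** "Main exposure variables that enter both models are mGFR at baseline, pre-existing frails, frailty-index, sex, BMI, age, comorbidities/medical history, medication, geriatric depression score", followed by quality of life. That is nine entries beside mGFR. Two of them, comorbidities and medication, are open-ended groups.
- **Interactions (same section).** One sentence covers two kinds. For the first kind, "Interaction terms will be used in model equations based on prior knowledge (evident interactions"), with none named. For the second kind, "other (currently unknown) interaction effects will be tested for a significant increase in the model performance". There is no candidate list, threshold, multiplicity correction or exploratory label. The separate event variables (dialysis, re-admission and so on) and their penalised regression come only in the next sentence.
- **Sample size.** The effect is the odds ratio of the 30-60 group against the >60 group, set at 1.75. "Statistical power was set to 80%, type I error rate was set to 5% and group imbalance is expected"; "Under these conditions one-sided testing led to the required sample size of 616 individuals to be analysed".

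**The concern.** The study has one primary question: whether the odds of frailty at 36 months are higher with mGFR 30-60 than with mGFR >60. The sample size treats the answer as one coefficient in a fixed model, tested one-sided at 5%. The analysis text allows the form of that model to depend on which interactions prove significant in the same data.

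Suppose a term mGFR × C enters, with C a covariate:

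logit P(frail) = b0 + b1·mGFR group + b2·C + b3·mGFR group·C, so OR(C) = exp(b1 + b3·C).

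There is then one odds ratio for each value of C. The main coefficient b1 describes only C = 0, which is the reference category of a binary covariate or the zero point of a continuous one. For age in years, that is age zero. This change of estimand happens under any coding.

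There is also a problem of inference. If the term entered because b3 was large by chance, b1 is displaced in the opposite direction by that chance value times the distance from C = 0 to the mean of C. An ordinary standard error takes no account of this selection.

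**Working it through.** **1. Which quantity the 5% belongs to.** Inputs from Sample size: frailty 20% and 12.5%, 40% of participants in the low-mGFR group (allocation ratio k = 1.5), 80% power, one-sided 5%.

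- OR = (0.20/0.80)/(0.125/0.875) = 1.75, as stated.
- Pooled proportion = 0.4 × 0.20 + 0.6 × 0.125 = 0.155.
- n(low) = [1.645·√(0.155·0.845·(1 + 1/1.5)) + 0.842·√(0.20·0.80 + 0.125·0.875/1.5)]² / 0.075² = (0.7685 + 0.4062)²/0.005625 ≈ 245.3, so 246.
- Total = 246 × 2.5 = 615, against 616 stated.

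Logistic-regression formulas give 609 to 622. Two-sided versions give 774 to 790 and do not match. Dividing by 0.75 for drop-out gives 616/0.75 ≈ 822, against 820. The stated N is therefore reproduced, and the 5% is the one-sided error of one mGFR coefficient in a fixed model. Expected frail participants: 616 × 0.155 ≈ 95.

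**2. Chance that a false interaction enters.** For m independent tests at 5% the chance is 1 − 0.95^m: 22.6% for m = 5, 33.7% for 8, 37.0% for 9 and 40.1% for 10. Simulation gave about 23-24%, 36% and 43% for 5, 8 and 10.

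**3. Effect on the mGFR coefficient.** Simulated logistic model with n = 616, 40% in the low-mGFR group, about 15% frail, true mGFR OR = 1 and no true interactions. Each mGFR-by-covariate product was kept if its likelihood-ratio p was below 0.05. The model was refitted with all kept terms, and the mGFR coefficient was tested one-sided at 5% with a 95% interval. Assumptions not in the plan: covariate log-odds 0.2-0.4, mild correlation of covariates with the mGFR group, and, for raw age and BMI, means 12 and 6 standard deviations from zero. Each row has 4,000 or 4,800 data sets, so the Monte Carlo standard error of the type I error is about 0.3 to 0.5 percentage points.

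| Covariate coding | Candidates | Type I error | 95% CI coverage |
|---|---|---|---|
| All centred | 5 | 5.2% | 94.9% |
| All centred | 10 | 5.6% | 94.2% |
| Half reference-coded binary, rest standardised | 5 | 6.4% | 93.2% |
| Half reference-coded binary, rest standardised | 10 | 8.2% | 89.8% |
| All but two reference-coded binary, two standardised | 5 | 7.6% | 91.6% |
| All but two reference-coded binary, two standardised | 8 | 9.4% | 88.8% |
| All but two reference-coded binary, two standardised | 10 | 9.8% | 88.0% |
| As the row above, age and BMI on raw scale | 5 | 11.6% | 84.1% |
| As the row above, age and BMI on raw scale | 8 | 13.5% | 81.2% |
| As the row above, age and BMI on raw scale | 10 | 13.5% | 81.7% |

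In the same data a fixed main-effects model gave 4.8-5.7% error and about 94-95% coverage. A separate run with nine candidates gave 6.6% and 91% with uncentred binary covariates, and 6.1% and 93.5% with all covariates centred.

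**4. Which interactions matter.** Adding all covariate-by-covariate products to the search (10 covariates, 1,488 data sets) meant that about 95% of data sets kept some term. Error and coverage hardly moved: 8.2% and 89.4% with reference coding, 6.0% and 93.1% centred. Only interactions that involve mGFR drive the loss.

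**The case against.** The strongest reply is that the sentence uses two different verbs. Interactions from prior knowledge are to be used in the equations, whereas unknown ones are only to be tested. A reader might infer that the plan expressly retains significant terms in the primary model, and it does not say that. This stands as a limit on the point. Retention is still the natural reading: both halves belong to one sentence about model equations, it follows the variable list for both models, and the criterion is better model performance.

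A second reply is that the size depends on coding, and the document gives none. This also stands. A reader might infer that the error rate at least doubles, but with all covariates centred it is almost nominal. Nor does testing more pairs in general make matters worse, as step 4 shows. I give no figure for lost power, because it would rest on covariate effects that the plan does not state.

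A third reply points to the elastic net or LASSO and the repeated cross-validation in the same section. They follow the sentence on event variables, and it is unclear whether they cover the primary model. They are described as controlling model size and overfitting, not as protecting the test or interval of the mGFR odds ratio. The article also does not say how standard errors will be obtained, so the simulated intervals assume ordinary ones.

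Finally, this is an observational cohort described in a condensed article, and an unseen analysis plan may fix the candidates, threshold and coding. Their absence is no fault. The point rests on the rule the article does state, which places a data-driven search inside the primary-model description.

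**Conclusion.** The point holds in a limited form. The plan sizes the study on one mGFR odds ratio at a one-sided 5% error, and then describes a significance-based search for interactions within the models that are to estimate it, with nothing to keep the two apart. If an mGFR interaction is retained, the single odds ratio ceases to exist, whatever the coding.

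The effect on error rates is a range, not a figure: about 5-6% error with coverage of about 93-95% if everything is centred, about 6-10% with 88-93% for reference-coded binary covariates, and about 12-14% with 81-84% for raw-scale age and BMI. This assumes that significant terms are kept, that 5 to 10 mGFR interactions are tried at 5%, and that ordinary Wald inference is used. The simulations cover the logistic model only. The documents do not establish where in the range the study would fall, so this is a defect to correct, not proof that the primary test will be invalid.

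**What to change.** State in Statistical methods that the primary mGFR odds ratio, its test and its interval come from a model with main effects plus only those interactions named before outcome data are seen, and name them. State that all other interactions are examined in a separate analysis labelled exploratory, with centred covariates and a correction for the number tested, and that its results do not alter the primary model. Apply the same rule to the Cox model.

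The cost is one or two sentences. The sample size of 616 analysed and 820 enrolled is unchanged. The downside is that a real but unforeseen interaction would be reported as exploratory only. There is time to do this before the primary outcome is available: recruitment opened on 2024-04-03, so the first 36-month assessments fall in April 2027.

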
### 4. Measurements

In the SHIP-AGE/MV-FIT study we will observe 820 participants over a period of 3 years. Informed consent will be obtained for participation in the study. Subjects who consent will be screened for eligibility and if the inclusion and none of the exclusion criteria are fulfilled, subjects will be enrolled. Data obtained from the screening, and enrollment visits must be supported in the patient’s source documentation, i.e. in the geriatric health record (eCRFs). Our follow-up (visits at 1st year and every 12 months) is designed to collect these data and to strengthen compliance to the individual interventions.

Screening Visits/Baseline: Adults aged 65 years or older will be enrolled if eligible. If eGFR (CKD-EPI) is known and >25 mL/min per $1.73\;{\text{m}}^{2}$, mGFR will be measured. Scheduled examination components and timeline by visits are shown in Fig 1.

Geriatric assessments and evaluations: Tables 1 and 2 show the assessments and evaluations. The GAITRite walkway system is the current gold standard in gait analysis. Leonardo mechanography, TUG, 5CRT are other physical measures.

**Table 1 pone.0324001.t001:** Frailty, renal function, and the effect of multi-component intervention strategies.

Design:	Prospective, longitudinal, observational study
All patient intervention:	Aerobic and resistance exercise and others (multi-factorial geriatric assessment monitoring and management systems)
Inclusion criteria:	Out-patients, aged ≥65 years, mGFR ≥30 mL/min per $1.73\;{\text{m}}^{2}$
Exclusion criteria:	Bedridden, palliative, inability to consent, severe dementia (MMSE<12), inability to speak, inability to fulfill at least 60% of the assessments
Primary outcome:	Frail vs. non-Frail
Secondary:	Frailty score transition (pre-frailty), mGFR transition, patient welfare, ability to live independently (off-dialysis), quality-of-life scales, burden of CKD on health status, cognitive decline, number of falls, admission to hospitals, referrals to nursing homes, all-cause mortality in primary care
Primary statistical method:	Multivariable logistic regression
Further statistical analysis:	Multivariable Cox regression, Chi-Square-Test, Propensity score matching

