### Study outcomes

The primary outcome will be frailty at 36 months post subject inclusion (i.e. Frail vs. non-Frail). Secondary endpoints are: Frailty score transition (pre-frailty), mGFR transition, patient welfare, ability to live independently, quality-of-life scales, burden of CKD on health status, cognitive decline, number of falls, admission to hospitals, referrals to nursing homes, all-cause mortality in primary care. Secondary endpoints will be determined using a broad spectrum of standard geriatric and research assessments as shown in Table 1 (for Abbreviations: see Table 2). Identification of novel parameters may be helpful for early detection of patients at risk for falls.

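### Dialysis, re-admission, nursing-home referral and death are analysed by logistic regression with no stated event window or allowance for person-time, while follow-up is given as three to about six years

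*Protocol article*

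**What the plan says.** Statistical methods assigns the clinical events to one method: "Event variables (obligation to dialysis, hospital re-admission, referrals to nursing homes, all-cause mortality, etc) will be analyzed with penalized multivariable logistic regression". The same section opens by describing what is counted: "The primary outcome Frail vs. non-Frail and events observed in the follow-up period will be analyzed using multivariable logistic regression". No horizon, offset or censoring rule follows for these events.

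The length of that period is described in different ways:

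- Eligibility criteria: "The planned minimum follow-up duration for participants is three years, while the maximum follow-up duration is approximately six years".
- Measurements: "In the SHIP-AGE/MV-FIT study we will observe 820 participants over a period of 3 years". The Abstract also gives three years, and the MV-FIT section gives 36 months for the incidence of frailty.
- Study outcomes fixes a horizon for frailty only: "The primary outcome will be frailty at 36 months post subject inclusion".

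Time-to-event analysis is tied to frailty: "multivariable Cox regression analysis will be conducted to study the time to frail", on condition that hazards are proportional. Table 1 lists "Multivariable Cox regression, Chi-Square-Test, Propensity score matching" as further analyses without saying which endpoints they serve.

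**The concern.** Logistic regression on whether an event was ever observed gives the same weight to a person watched for three years and one watched for six. Two consequences follow.

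First, the odds ratio has no defined horizon, because it averages over whatever lengths of follow-up occurred.

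Second, if the two mGFR groups are observed for different lengths of time, the difference enters the odds ratio as an apparent CKD effect or hides a real one. The protocol offers several routes to such a difference. CKD patients are also sought through local nephrologists, so their enrolment dates may differ. The planned 25% drop-out includes deaths. Death before dialysis, re-admission or nursing-home referral ends the chance of observing that event, and the Introduction itself describes CKD as a leading risk factor for all-cause mortality.

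The allocation of methods is also unexpected. Frailty, assessed at 12-monthly visits, gets a Cox model, whereas death, which has a definite date, gets none that is clearly assigned to it.

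**Working it through.** **1. Follow-up range from the protocol's own dates.** Recruitment runs from 2024-04-03 to 2025-09-30 (General design), and estimated completion is 2030-09-30 (Study timeline). Entry on the first day allows 6.5 years and entry on the last day 5.0 years. This does not match three to six exactly and may include closing work, but on either account the length varies between persons.

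**2. Model.** The protocol gives no rates for these events, so a constant hazard h is assumed. Risk by time t is 1 − exp(−ht). With the same hazard in both groups (no true effect), mean observation times t₁ and t₂ give

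OR = [exp(ht₁) − 1] / [exp(ht₂) − 1].

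**3. Half-year difference, centred on 4.5 years (4.75 v 4.25).** At h = 0.04 the risks are 17.3% and 15.6%.

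| h per year | OR |
|---|---|
| 0.03 | 1.126 |
| 0.04 | 1.129 |
| 0.05 | 1.132 |

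If the shorter time falls in the CKD group, the OR is 0.88 to 0.89.

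**4. How large an enrolment gap is possible?** Inputs: 505 enrolled by 2025-03-05 (Status of study), a target of 820, and an expected 492 with mGFR above 60 and 328 with mGFR 30–60. Assume even accrual before and after that count and a common closing date. In the extreme case where all 492 enter before any of the 328:

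- The first 505 enter over 336 days (0.92 years) and the other 315 over 209 days (0.57 years).
- Mean entry of the first 492: 0.92 × (492/505) / 2 = 0.45 years.
- Mean entry of the last 328: 1.19 years.
- Difference: about 0.75 years.

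Centred on 4.5 years (4.875 v 4.125), the OR is 1.195, 1.200 and 1.205 at h = 0.03, 0.04 and 0.05, or 0.83 to 0.84 in the other direction. With the calendar dates themselves (6.04 v 5.30 years) it is 1.15 to 1.16. Overlapping entry gives less.

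**5. Drop-out.** Assume 35% drop-out in the CKD group and 18.3% in the other (0.4 × 35% + 0.6 × 18.3% = 25%), spread evenly over three years, with drop-outs coded as non-events. At a 3-year risk of 12.5%, a drop-out's mean observed risk is 6.4%. The observed risks are then:

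- CKD group: 0.35 × 6.4% + 0.65 × 12.5% = 10.4%
- Other group: 0.183 × 6.4% + 0.817 × 12.5% = 11.4%

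The null OR is 0.90, and it is 0.89 to 0.91 over 3-year risks of 5 to 30%.

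**6. Equal follow-up in both groups.** Under the null the OR is 1. With an assumed hazard ratio of 1.75 (a figure borrowed from the frailty OR), the OR depends on the horizon:

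| 3-year reference risk | OR at 3 y | OR at 4.5 y | OR at 6 y |
|---|---|---|---|
| 5% | 1.78 | 1.80 | 1.82 |
| 12.5% | 1.84 | 1.89 | 1.95 |
| 30% | 2.02 | 2.19 | 2.39 |

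The mixing of horizons is therefore minor for rare events and matters for common ones such as hospital admission.

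**The case against.** The strongest reply is that a common 36-month window is intended. Several sections speak of three years, and the follow-up period in Statistical methods could mean just that. A condensed article may also leave event windows to a fuller plan, and Table 1's Cox entry is not restricted to frailty. This makes the intention uncertain. It does not settle it, because no section limits the event endpoints to 36 months, the three-to-six-year statement stands beside the others, and the article does name a method for these events.

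A reader might infer more than the documents support:

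- **A twofold false effect.** At 4% per year, six years against three gives an OR of 2.13. That compares everyone at six years with everyone at three. It is not a contrast between mGFR groups.
- **CKD patients enrol later.** The protocol says nephrologists will be contacted. It does not say when.
- **Drop-outs are coded as non-events.** This is not stated. The text mentions imputation to complete the data, so step 5 is an assumption.
- **Competing death affects every endpoint.** It applies to the non-fatal events only, since for all-cause mortality death is the outcome.
- **Penalisation invalidates the CKD estimate.** Regularisation by elastic net or LASSO is given a generalisability purpose, and the sentence on the primary model names no penalty. The point matters only if a penalised coefficient is read as the CKD effect.

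**Conclusion.** The point holds for the secondary event endpoints. The stated method makes no allowance for unequal observation time, and the protocol's accounts of follow-up length do not agree. The primary frailty outcome has a fixed 36-month horizon and is not affected.

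The missing window is certain from the text; the bias is conditional. It arises only if observation time differs by mGFR group. At assumed constant hazards of 3 to 5% per year, a half-year gap moves a null OR to about 1.13, and the extreme enrolment gap of about 0.75 years moves it to about 1.2. That upper figure rests on even accrual and covers enrolment timing alone; differential drop-out or death would come on top, in either direction. For scale, the frailty effect used for the sample size is an OR of 1.75. If follow-up is alike in both groups there is no false positive effect, only an odds ratio without a clear horizon.

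**What to change.** First, reconcile the three-year and the three-to-six-year statements. Then choose one of two routes for the event endpoints:

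- **Fixed window.** Count each event within 36 months of inclusion for everyone, with a stated rule for deaths and drop-outs. Logistic regression can then stay. The cost is the loss of later events.
- **Time-to-event.** Use Cox regression for death, and cause-specific hazards with cumulative incidence (death as the competing event) for dialysis, first re-admission and nursing-home referral. For counts of falls and admissions, use a count model with a log person-time offset.

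The second route needs event dates. Table 2 lists numbers of falls, hospitalisations and nursing-home stays, and visits are annual; the article does not say that dates are captured. The sponsor should confirm this, because otherwise the route requires extra data collection.

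Where a penalised model is used to estimate the CKD effect, leave the mGFR term unpenalised.

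Apart from the possible need for dates, the cost is wording and slightly more analysis work. At the article's status date of 2025-03-05, participants could have been followed for at most 0.92 years from the start of recruitment, so the change could be made well before any 36-month outcome exists.
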